**Methods:**

The STOP-ACEi trial (trial registration: current controlled trials, ISRCTN62869767) is an investigator-led multicentre open-label, randomized controlled clinical trial of 410 participants with advanced (Stage 4 or 5) progressive CKD receiving ACEi, ARBs or both. Patients will be randomized in a 1:1 ratio to either discontinue ACEi, ARB or combination of both (experimental arm) or continue ACEi, ARB or combination of both (control arm). Patients will be followed up at 3 monthly intervals for 3 years. The primary outcome measure is eGFR at 3 years. Secondary outcome measures include the number of renal events, participant quality of life and physical functioning, hospitalization rates, BP and laboratory measures, including serum cystatin-C. Safety will be assessed to ensure that withdrawal of these treatments does not cause excess harm or increase mortality or cardiovascular events such as heart failure, myocardial infarction or stroke.

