#### Safety

Safety of intervention related to potential harm (e.g. increased cardiovascular events such as heart failure, myocardial infarction, stroke or death, participant survival in each group)

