### Statistical considerations

#### Sample size

An observational study provided data on eGFR in 52 patients with advanced CKD in the 12 months prior to stopping ACEi/ARB treatment, at the point of stopping ACEi/ARB and 12 months after stopping (Table 2) [31]. These data form the basis of the sample size calculation.

**Table 2. GFV346TB2:** Data that formed the basis of the sample size calculation

Time point relative to stopping ACEi/ARB	eGFR (mL/min/1.73 m^2^), mean ± SE (SD)
−12 months	22.9 ± 1.4 (10.1)
0	16.38 ± 1 (7.2)
+12 months	26.6 ± 2.2 (15.9)

eGFR in patients with CKD who underwent ACEi/ARB withdrawal in a previously published study.

To err on the side of caution, the largest standard deviation was used to estimate the variability in eGFR (i.e. SD of 16 mL/min/1.73 m^2^) for the sample size calculation. To detect a minimum relevant difference between groups of 5 mL/min/1.73 m^2^ (i.e. effect size of 0.31) with 80% power and alpha = 0.05 (using a two-sample *t*-test), a total of 410 participants (205 per group) will need to be recruited (this includes allowance for 20% dropout). Data from Beddhu *et al*. who used propensity scores in a multivariate model in Dialysis Morbidity and Mortality Study Wave 2 patients showed that each 5-mL/min fall in MDRD GFR was associated with an increased hazard of death in a multivariable Cox model (HR 1.14; P = 0.002) [44].

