#### Statistical analysis

The Statistical Analysis Plan will describe the planned analyses for STOP-ACEi in full detail. A summary of the main analyses are given here. All analysis will be based on the intention to treat principle, and a P-value of <0.05 will be considered statistically significant. The primary outcome is the continuous measure eGFR at 3 years. These data will be summarized using means and standard deviations, with differences in means and 95% CIs reported. The two groups will be compared at 3 years using both a two-sample *t*-test and ANCOVA to adjust for baseline values. Longitudinal plots of the data over time will be constructed for visual presentation of the data. As a secondary analysis, a repeated measures analysis, including a treatment by time cross-term, will be carried out on all data across the 3 years of follow-up.

Continuous secondary outcome measures (e.g. BP, quality of life) will be analysed in the same way as the primary outcome. Categorical (dichotomous) outcome measures (e.g. hospitalization rates) will compare the proportion of participants and percentages using a χ^2^ test, with relative risks and 95% CIs reported. Time-to-event outcomes (e.g. time to ESRD, mortality) will be analysed using survival analysis and log-rank methods. Kaplan–Meier survival curves will be constructed for visual presentation of time-to-event comparisons. Treatment effects will be expressed as HRs with 95% CIs.

Several *a priori* subgroup analyses with respect to the minimization variables for both primary and secondary outcomes will be performed. These analyses will be considered hypothesis generating.

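### All-cause hospitalisation is named as a rate, but the stated analysis is a chi-squared test of ever versus never admitted, which drops repeat admissions and uses no time at risk

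*Protocol article*

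**What the plan says.** In the protocol article, under Secondary outcome measures (Clinical events), the outcome is a rate of hospitalisation from any cause. The abstract and the discussion also speak of hospitalisation rates.

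The Statistical analysis section gives it as the example of a dichotomous outcome: "Categorical (dichotomous) outcome measures (e.g. hospitalization rates) will compare the proportion of participants and percentages using a" chi-squared test, "with relative risks and 95% CIs reported". Survival methods are reserved for another class: "Time-to-event outcomes (e.g. time to ESRD, mortality) will be analysed using survival analysis and log-rank methods". Hospitalisation is not among those examples, and no count, person-time or time-to-first-admission analysis of it is stated anywhere.

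On follow-up, "Patients will be followed up at 3 monthly intervals for 3 years". The sample size paragraph expects some of it to be incomplete ("this includes allowance for 20% dropout"), and death is tracked by arm as a safety outcome ("stroke or death, participant survival in each group").

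**The concern.** A rate is events per unit of time, whereas a proportion ever admitted is a different quantity with a different effect measure. The article fixes the outcome type, the test and the effect measure, so the mismatch lies in what it states and not in detail left to the analysis plan.

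Two losses follow by construction. A participant admitted five times counts the same as one admitted once. A participant who leaves follow-up early without an admission supplies no information on how short the exposure was.

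The first loss costs power and pulls the reported relative risk towards 1 compared with the rate ratio. The second can distort the comparison if one arm loses clearly more person-time, because that arm has less opportunity to be admitted and may look better. This matters because the discussion counts hospitalisation among the clinical outcomes that stopping treatment might improve.

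**Working it through.** **The article's own figure.** The only design figure is for the primary outcome: "a total of 410 participants (205 per group) will need to be recruited". With a difference of 5, SD 16, 80% power and two-sided alpha 0.05 (sidedness assumed), the normal formula gives n = 2 × (1.960 + 0.842)² × 16² / 5² ≈ 161 per arm. Then 161 / 0.80 gives 202 per arm, 404 in total. The exact t-test with the rounded effect size 0.31 gives 164.3 / 0.80 = 205.4 per arm. The figure of 410 therefore reproduces, and this point does not touch it. No figure is stated for hospitalisation.

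**Inputs.**
- From the article: n = 205 per arm, 1:1 allocation, T = 3 years.
- Assumed, because the article gives none: control rate λ = 0.5 to 1.0 admissions per person-year, rate ratio 0.75, gamma frailty with variance k = 0.8, exponential death h = 0.07 per year in both arms.

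**Step 1: exposure and mean count.** Mean follow-up is (1 − e^(−hT))/h = (1 − e^(−0.21))/0.07 = 2.706 years. Mean admissions per control are 0.5 × 2.706 = 1.35 up to 1.0 × 2.706 = 2.71. The planned test uses at most one of these.

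**Step 2: proportion ever admitted.** For follow-up t this is 1 − (1 + kλt)^(−1/k), averaged over the follow-up distribution.

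| Control rate | Ever admitted, control | Ever admitted, rate ratio 0.75 | Relative risk |
|---|---|---|---|
| 0.5 | 0.583 | 0.510 | 0.88 |
| 1.0 | 0.739 | 0.679 | 0.92 |

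The same rate ratio of 0.75 thus appears as a relative risk of 0.88 or 0.92, depending on how common admission is.

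**Step 3: power of the chi-squared test.** Power ≈ Φ[(d − 1.96 × SE0)/SE1], where d is the difference in proportions, SE0 its standard error under the null and SE1 under the alternative.
- λ = 0.5: d = 0.0725, SE0 = 0.0492, SE1 = 0.0490, so Φ(−0.49) = 31%.
- λ = 1.0: d = 0.0604, SE0 = 0.0449, SE1 = 0.0448, so Φ(−0.62) = 27%.

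**Step 4: power of a rate analysis of the same data.** The variance of the log rate ratio is the sum over arms of 1/(n × mean count) + k × E(t²)/(n × E(t)²), with E(t²) = 7.834. The second term is 0.8 × 7.834/(205 × 2.706²) = 0.00418 per arm.
- λ = 0.5: 0.00361 + 0.00481 + 2 × 0.00418 = 0.0168, SE 0.1295. Since |ln 0.75| = 0.2877, power = Φ(0.2877/0.1295 − 1.96) = Φ(0.26) = 60%.
- λ = 1.0: 0.00180 + 0.00240 + 2 × 0.00418 = 0.0126, SE 0.1121. Power = Φ(0.61) = 73%.

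Simulation with the same inputs gave about 28–33% for chi-squared and 62–73% for the rate test, in line with these approximations. Over a wider range (0.3 to 1.0 admissions per year, frailty variance 0.5 to 1.0), it gave 24–39% and 45–86%.

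**Step 5: equal admission rates, unequal death.** With λ = 0.5 in both arms and death at 0.05 versus 0.10 per year, mean follow-up is 2.79 versus 2.59 years and the proportions ever admitted are 0.595 versus 0.565. The shift is 0.0295/0.0488 = 0.60 standard errors, so the rejection probability is Φ(0.60 − 1.96) + Φ(−0.60 − 1.96) ≈ 9%. Simulation gave about 10%. Other simulated settings:

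| Yearly loss or death by arm | Chi-squared | Rate test |
|---|---|---|
| 7% v 7% | about 5% | about 5% |
| 5% v 6% | 5.5% | near 5% |
| 7% v 8.5% | 6.0% | near 5% |
| From 5% v 10% up to 5% v 15% or 10% v 20%, λ 0.3 to 0.8, k 0.5 | 9–31% | 4–6% |

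**The case against.** Hospitalisation rate is often used loosely for the percentage hospitalised, and the analysis section says outright that proportions will be compared. The proportion ever admitted within a fixed 3 years is a well-defined quantity, and a chi-squared test of it is valid for participants whose status is known. The rejection rates in Step 5 are excess only against a null of equal rates. The article is also a summary that defers full detail to an analysis plan not shown here. This is one secondary outcome among several, and deaths are reported separately, so an excess would be visible beside any apparent fall in admissions.

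Most of this stands as a limit on weight. It does not remove the mismatch: the outcome is named a rate, and the article itself fixes a test that cannot estimate one.

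A reader might also infer four stronger things that the documents do not support:
- **Ever/never is close to its ceiling.** Under the assumptions above about 58–74% of controls are ever admitted. The power is lost by ignoring repeat admissions, not through a ceiling.
- **The test is biased whenever death or dropout differs.** Small differences barely move it. The problem becomes material only when the arms differ substantially, and the safety reporting section expects no significant excess risk from withdrawal.
- **Early deaths will be counted as if followed for 36 months.** The article states no rule for deaths or withdrawals in this outcome, and such rules commonly sit in the analysis plan.
- **Admissions are already recorded at every visit.** The schedule of assessments lists adverse event documentation and has no hospitalisation item.

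**Conclusion.** The point holds as a mismatch between the named outcome and the stated analysis. The planned test does not estimate a hospitalisation rate, discards repeat admissions and uses no time at risk. Under the assumed inputs it has roughly half the power of a rate analysis or less (about 28–33% against 62–73% at a rate ratio of 0.75). Its rejection rate as a test of rates rises to about 10% if yearly deaths are 5% versus 10%, and stays near 5% if losses are similar. The admission rate, overdispersion, death rates and rate ratio are all assumptions, so the sizes are illustrative; the direction of the power loss held throughout the range examined. The change is worth making, but the trial's main conclusion does not depend on it.

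**What to change.** In the Statistical analysis section, take hospitalisation out of the dichotomous class. Analyse all-cause admissions as counts by negative binomial regression (or Poisson with robust standard errors) with log follow-up time as offset. Report the rate ratio with 95% CI, show deaths by arm alongside, and keep the proportion ever admitted as description.

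Alternatively, if the proportion is what is wanted, rename the outcome as the proportion ever hospitalised and analyse time to first admission with death as a competing event. This removes the mismatch but still uses only first admissions.

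The cost is a little more analysis work. The sponsor should also confirm that every admission and its date are captured through adverse event reporting, since neither the schedule of assessments nor the safety reporting section says so. The change is best made before outcome data by arm are seen; the article reports 118 of 410 participants (29%) recruited at the time of writing.

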## MONITORING

### Safety reporting

It is expected that the risk of the trial intervention, withdrawal of ACEi and/or ARB, will not be significantly higher than that of standard medical practice. The incidence of adverse events, including cardiovascular events, will be closely monitored by the trial oversight committees. All adverse events will be reportable to the STOP-ACEi trial office until each participant's final assessment at 3 years.

### Data monitoring committee

A DMEC will independently monitor the efficacy and safety analysis reports at least annually. The independent members of this committee are [name] (Consultant Nephrologist; chair), [name] (Consultant Cardiologist) and [name] (Statistician).

## REGULATORY ASPECTS

The RCT will be conducted according to the standards of the International Conference on Harmonisation-Good Clinical Practice (GCP) and the Research Governance Framework for Health and Social Care. Pharmaco-vigilance reporting will comply with the Medicines for Human Use (Clinical Trials) Regulations 2004 and Amended Regulations 2006. Written informed consent will be provided by all patients prior to randomization and any study-related procedures.

STOP-ACEi is sponsored by the Hull and East Yorkshire Hospitals NHS Trust (R1578). The Medicine and Healthcare Products Regulatory Authority clinical trial authorization reference is 21411/0242/001-0001. The EudraCT number is 2013-003798-82.

## ETHICAL COMMITTEE APPROVAL

Ethical approval for STOP-ACEi was granted by the National Research Ethics Service Committee Yorkshire and the Humber—Leeds East (13/YH/0394) on 29 January 2014.

## DISCUSSION

Studies on the effects of ACEi/ARB in advanced CKD are lacking. In addition, published studies have failed to dissociate the putative renoprotective effects that are specific for ACEi/ARBs from their antihypertensive effect. Also, the benefits of the association between reducing protein excretion and the doubling of serum creatinine have recently been challenged by clinical trials such as ACCOMPLISH and ONTARGET, where a reduction in proteinuria/albuminuria was associated with accelerated CKD decline. The results of STOP-ACEi will provide evidence on whether discontinuation of ACEi/ARB is beneficial to renal function (improvement/stabilization) and improves other important parameters including laboratory (hyperkalaemia, anaemia) and clinical outcomes (hospitalization rates, physical function and quality of life) without causing an increase in cardiovascular events. It aims to clarify whether the benefits of this intervention outweigh the risks. It is, therefore, hoped that this pivotal study can provide new findings to allow future consideration of a large randomized controlled trial with mortality outcomes in this important group of patients.

### Trial status

STOP-ACEi opened to recruitment on 2 July 2014, and the first patient was recruited on 11 July 2014. As of 11 Sep 2015, 118 patients (29%) were recruited into the study.
